**Health Information Technology Evaluation and Support Center**

**Multisite Evaluation Protocol**

1. **Synopsis**

The Health Information Technology Evaluation and Support Center (HITEC) is a center to support demonstration projects implementing and evaluating electronic network systems as part of the Special Projects of National Significance (SPNS) Initiative on Information Technology Networks of Care. Electronic network systems are comprised of computer hardware and software programs that permit the electronic exchange of health information among providers at different points of service, thereby improving the continuity and quality of care. HITEC will provide leadership in the design, implementation, and evaluation of such electronic network systems among providers serving people living with or affected by HIV/AIDS in underserved communities. This will be accomplished using both qualitative and quantitative methods. Qualitative, key informant interviews will help characterize the clinical settings, providers, and patients at the demonstrations sites funded under this Initiative; and contextualize the barriers, facilitators, and circumstances that affect the implementation of electronic network systems at these sites. Quantitative patient and provider surveys, as well medical records reviews, will be used to collect common indicator variables at all sites in order to measure the implementation of the network systems and their impact on patient care. The primary goal of these mixed methods is ensure that the evaluation of electronic network systems has maximum impact on the theory, practice, and policy of delivering HIV health services. In addition, HITEC will provide training and support to sites implementing and evaluating electronic networks. This will be accomplished through site visits, grantee meetings, in-person trainings, and ongoing technical assistance. The work of HITEC will be conducted by a multidisciplinary team led by the Center for AIDS Prevention Studies (CAPS) at the University of California, San Francisco (UCSF).

1. **Hypothesis**

As an evaluation center, this work will be guided by a set of evaluation questions, as opposed to scientific hypotheses. These questions are:

1. What are major barriers—technological, attitudinal, financial, and structural—to the implementation of electronic network systems in Ryan White Program-funded clinics?
2. What characteristics of electronic network system technology are associated with improved decision-making and greater satisfaction among clinical providers?
3. What characteristics of electronic network systems and the clinics in which they are used are associated with cost-effective improvements in patient treatment outcomes, such as linking to care at an earlier stage in HIV disease, better tracking of HIV disease progression indicators, and better tracking of referrals to care?
4. What are the characteristics of patient populations that are more receptive to the use of health information technology in clinical settings?

How do electronic network systems enhance linkages between local clinics and public health architectures, such as facilitating the completion of Ryan White Program reports?

1. **Specific Aims**

- Aim 1 (Evaluation): To facilitate and conduct rigorous evaluation across demonstration sites that has maximum impact on the practice and policy of using electronic network systems in settings that provide care and support for people living with or affected by HIV.
- Aim 2 (Support and Training): To provide methodological (both quantitative and qualitative) research design and evaluation consultation and support to proposed demonstration projects; to offer technical assistance on the implementation of electronic network systems in HIV care settings; to assist sites in the design of state-of-the-art data collection and management systems; and to provide a central database for the measurement of outcomes.
- Aim 3 (Dissemination): To synthesize and disseminate findings from demonstration projects so that they have optimum impact on the research, practices, and policies of electronic network systems.
- Aim 4 (Capacity): To stimulate innovative projects and ensure scientific excellence, as well as support organizational capacity to ensure integrity of research and sound fiscal operations.

1. **Background and Significance**

Interest has grown in the application of computer technology to health information, including the use of electronic network systems, because research has documented the potential for success. A recent review of published articles on computer technology in primary care settings found evidence that it can improve the management of chronic diseases, increase the rate with which preventive medical tasks are completed (e.g., vaccinations), increase the prescription of generic drugs, and promote cost savings and the administration of fewer unnecessary tests.^9^ More recent research has continued documenting these successes by showing that computer technology leads to better recording of the clinical indicators of chronic conditions,^10^ better patient outcomes for hypertension,^11, 12^ fewer red blood cell transfusions and associated costs,^13^ and an increase in the quality of nursing by promoting more direct interaction time with patients.^14^

Electronic network systems have the ability to connect health information with providers, patients, and public health agencies, which could be particularly valuable in the area of HIV care. By its very nature, HIV disease is complex, affecting patients’ health and well-being in multiple ways. As such, promoting the communication of information among various specialized providers could enhance greatly patient care in a number of domains:

**Diagnosis.** The advantages of electronic technology may start as early as the identification of disease. Research has documented systematic disparities in the diagnosis of HIV disease, with ethnic minorities and women receiving their diagnoses later than Whites and men.^15-19^ When examined retrospectively, research has found that many patients pass through the medical care system with evidence of HIV transmission risks and yet are never screened.^20-22^ This phenomenon occurs in part because seroconversion symptoms are often misdiagnosed ^23-26^ or because such symptoms are absent altogether.^26^ However, recent research has demonstrated that it is possible to improve the likelihood of identifying patients with very recent infections. By collecting information on specific clinical features commonly associated with HIV seroconversion, patients at highest risk of having new infections can be accurately identified and offered HIV testing.^27^ Electronic network systems could aid this goal by allowing providers to record clinical and behavioral information related to possible HIV seroconversion, and then by generating electronic reminders for testing when patients are at high risk of infection.

**Treatment.** Electronic technology will likely be beneficial in the ongoing treatment of the disease. For many of the most vulnerable communities affected by HIV, referrals to care are a critical challenge. For example, research with homeless and low-income populations has shown that structural and individual barriers often prohibit access to services even when care is desired.^28-33^ To achieve improvements in health in these marginalized populations, one needs active outreach efforts and coordinated care.^34-37^ Electronic network systems would allow for improved continuity of care and referrals by enabling one to transmit needed medical information directly and instantly, without having to rely on courier services or the patient to carry it; store critical tracking information to help locate difficult-to-reach patients; and allow one to determine whether a patient actually acts on a referral. Electronic network systems also would enable providers to determine when critical tests were conducted last, to access the results of those tests regardless of whether or not they occurred in the office where the provider works, and to ensure that further care is delivered in a timely manner. For example, in prior research, electronically-generated reminders based on patient records reduced significantly the amount of time that elapsed before a provider ordered a needed CD4 test or prescribed antiretroviral medications to individuals with declining immune function.^38^

**Preventing Transmission.** Increasing emphasis is being placed on clinic-based efforts to work with patients to limit the likelihood of disease transmission.^39, 40^ These “Prevention with Positives” initiatives face a number of challenges, including a lack of relevant provider training,^3, 41^ insufficient time,^3, 42^ a belief that prevention efforts will fail,^5^ and systematic disparities in the delivery of such care.^4, 41-43^ However, other research has shown that relatively brief, patient-tailored, clinician-delivered prevention messages can significantly reduce sexual risk behaviors.^44^ Electronic network systems can collect relevant behavioral risk data from multiple sources to help clinicians tailor risk reduction messages. Furthermore, electronic network systems can contribute to partner notification efforts by transmitting patient-volunteered partner information to individuals who will work with the patient on disclosing his or her infection.

**Challenges to Implementation**

The application of electronic technology to health information is still relatively new and faces barriers to wide adoption. Little research has focused specifically on barriers to electronic network systems, but investigators have examined the obstacles to computer technology more generally.^6^ In particular, there are four important barriers that likely impact the acceptability and adoption of electronic network systems:

1. Cost (both in terms of finances and personnel). Electronic network systems require an initial investment in hardware, networking, and provider and staff training. There are reports of primary care training centers discontinuing the use of computer-based systems because the investments required were too burdensome.^45^
2. Data security. The Health Insurance Portability and Accountability Act (HIPAA) of 1996 has strict standards to protect patient information, and limits to whom such information can be disclosed. An electronic network system must have sufficient data encryption and firewall protections to ensure that patient information is not compromised. Furthermore, users of the system must ensure that the protocols for sharing and accessing patient information within the network are in compliance with HIPAA regulations.
3. Attitudes toward electronic network systems. Many providers have concerns about the time and training that are required to learn to use new programs.^9, 46^ Patients have voiced concerns about the security of the data in computer systems,^47, 48^ and even indicated an unwillingness to see providers whom they knew were entering medical information into such systems.^49^ Privacy concerns are especially important around HIV, which is often still stigmatized.^50^
4. Program compatibility.^6, 51^ To be useful, electronic data collected in one computer application must be readable by the other applications in use in different provider offices. If compatibility is lacking, use of the system or favorable opinions about it may lag.

*Summary*

Electronic network systems are a promising and important component of health information technology. Such systems could improve diagnosis, treatment, and prevention efforts with HIV-infected clients, and may enhance policy development at a national level. However, there remain significant barriers to the adoption of these systems, which could undermine the uptake and use of electronic technology. A thorough evaluation would help ensure that electronic systems are implemented in a manner that maximizes the likelihood of success.

1. **Design**

HITEC’s evaluation consists of five key components displayed below. The HRSA-sponsored Initiative (for which HITEC is the evaluation center) is nearing the end of Year 2. Assessments described as occurring “Before ENS Rollout” are nearly completed. After ENS rollout, HITEC is continuing to collect follow-up data in six month intervals for two years, until approximately September, 2010. The final year of the Initiative (Sept. 2010- Aug. 2011) will be dedicated to data analysis and dissemination.

| **Method** | **Population** | **Sample size/**  **Demonstration Site** | **Time frame** |
| --- | --- | --- | --- |
| **Key Informant interviews (Component 1)** | Project Staff and Key Collaborators | Up to 7 | Before ENS rollout and late in Year 3 of Initiative |
|  | Users of the ENS | Up to 10 | Before ENS rollout and late in Year 3 Initiative |
|  | Patients | Up to 10 | In Year 3 of Initiative |
| **Surveys**  **(Component 2-4_** | Systems survey  (Component 2) | 1 survey completed for each site per wave (completed via combined interview with project director and network administrator) | Before ENS rollout, every 6 months after rollout, at the end of Initiative |
|  | Users Survey (Component 3) | Entire population (about 20 at most sites) | Before ENS rollout and every 6 months after rollout |
|  | Patients Survey  (Component 4) | 100 | Before ENS rollout and every 6 months after rollout |
| **ENS data abstraction (Component 5)** | Patients | 100 | Before ENS rollout and every 6 months after rollout |

Key informant interview capture data that speak to the facilitators and barriers to implementation of the ENS. The systems, users, and patients survey, as well as the ENS data abstraction, capture quantitative data that allow HITEC to examine the system, user, and patient characteristics associated with the greatest improvements in clinical care and health outcomes.

1. **Statistical Analysis**

**Key Informant Interviews:** Qualitative data will be evaluated by our team of research analysts, using a method for codebook development and validation that has been developed over years of work with similar projects and populations. The procedures we use are as follows: First, all interviews are tape-recorded and transcribed. If an interview is conducted in Spanish, it is translated into English before transcription. Second, analysts read a cross-section of the interview transcripts and establish a preliminary codebook. Third, the preliminary codebook is applied to a sub-set of interviews. As each analyst attempts this process, he or she modifies the codes to reflect further nuances in conceptual categories. After preliminary coding is complete, the analysts meet and settle on a final set of codes. Fourth, every interview transcript is read independently by two analysts who apply the final codes to the text. The analysts then meet to compare their codes. Disagreements are resolved by discussion to reach consensus. *Atlas.ti*^52^ is used to facilitate all coding work.

Once coding is finished, analysts then examine the complete set of interviews to identify convergent and divergent themes that have emerged across various conceptual categories. For example, analysts might examine the similarities and differences in facilitators and barriers to electronic network systems across demonstration sites, types of providers, or target populations.

**Quantitative Data Analyses (includes data collected via the systems survey, user survey, patient survey, and ENS data extraction):**

***Analyses will be organized around a series of objectives:***

**Quantitative Objective 1. *To assess whether Electronic Network Systems (ENS) improve the quality of care, satisfaction with care, and patient health outcomes.***

We will present descriptive analyses of the quality of HIV care, support services, and patient health outcomes over the project period (graphs, etc.). We also will assess changes in the quality of HIV care, support services, and patient outcomes using both descriptive analyses and mixed models to adjust for baseline differences in each outcome across the six ENS and to account for the covariance of outcomes within each ENS.

**Quantitative Objective 2.  *To assess what characteristics of the ENS are specifically associated with improvements in care, satisfaction, and health outcomes.***

Data collected as part of the “systems” assessment will allow us to characterize the components, functions, and data of the six ENS systems. We will present descriptive analyses that demonstrate the relationship between specific ENS characteristics and outcomes in quality of care, patient satisfaction, and health status. Whenever possible, we will categorize the six ENS into subgroups based on common characteristics and examine via descriptive analyses the associations of the subgroups with clinical outcomes.

**Quantitative Objective 3.** ***To assess how user and patient characteristics and attitudes mediate and/or moderate changes in outcomes.***

We specifically expect that ENS, user, and patient characteristics will influence users’ attitudes about the system. These attitudes in turn will affect actual system usage, which will affect health care service delivery and, ultimately, health outcomes. Relationships between individual variables can be documented via correlations or via regression equations. Potential mediation can be examined by regressing outcomes variables (e.g., health care service delivery) onto predictor variables (e.g., user attitudes) in models that include and exclude potential mediators (e.g., actual system usage). If the mediator is in fact responsible for the relationship between the predictor and the outcome, then the regression weight for the predictor will be reduced significantly whenever the mediator is included in the regression model. Potential moderation can be examined by including interaction terms in regression models. If we have sufficient power, the overall quality of the conceptual model can be tested using structural equation modeling.

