For the **user survey**, we will seek to interview the entire population of users at the sites. The exact number of users differs by site, but is an average of about 20. The same users will likely be assessed across waves. However, if all users are unique at each wave, then the total number of people interviewed will be **up to 600 unique individuals** (20 people per site per wave; six sites; five waves). Because the total population of users at each site is relatively small, we are seeking to survey them all in order to maximize statistical power for analyses. Users will enrolled as participants at UCSF.

For the **patient survey**, we will seek to interview 100 individuals per wave. If all individuals are unique at each wave, then we may survey **up to 3000 unique individuals** (100 people per site per wave; 6 sites; 5 waves). A sample of 100 per site (N=600 per observation period) will give us 80% power to detect 10% change in proportional outcomes (e.g. 50% to 60%) in the underlying popluation using a two-sided test with 0.05 alpha. This estimate assumes an intra-class correlation (ICC) of 0.005. ***Participants in this survey (except pilot test subjects) will be enrolled at the local sites via procedures approved by the local IRB. UCSF will only receive de-identified data for secondary analyses.***

For the **ENS data extraction**, we will seek to obtain de-identified data on 100 individuals per wave. (Note: these individuals do NOT have to be the same people who participate in the patient survey.) If all individuals are unique at each wave, then we may obtain data on **up to 3000 people** (100 people per site per wave; 6 sites; 5 waves). A sample of 100 per site (N=600 per observation period) will give us 80% power to detect 10% change in proportional outcomes (e.g. 50% to 60%) in the underlying popluation using a two-sided test with 0.05 alpha. This estimate assumes an intra-class correlation (ICC) of 0.005.. ***Data extraction is conducted at the local sites via procedures approved by the local IRB. UCSF will only receive de-identified data for secondary analyses.***

**If every participant were unique (across all components), then up to 6936 individuals could contribute data to the study.**

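### Objective 3's only mediation criterion, a significant fall in the predictor's weight, can miss partial mediation if logistic models are used and cannot by itself separate mediation from confounding

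*Protocol*

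**What the plan says.** Under Quantitative Objective 3 (Protocol, Statistical Analysis), a chain is expected: characteristics of the system, users and patients shape user attitudes, attitudes affect usage, and usage affects service delivery and finally health outcomes. The method is: "Potential mediation can be examined by regressing outcomes variables (e.g., health care service delivery) onto predictor variables (e.g., user attitudes"). Each regression is fitted both with and without a candidate mediator, for which actual usage of the system is the example. The criterion is conditional on the mediator truly accounting for the link from predictor to outcome; the consequence drawn is: "then the regression weight for the predictor will be reduced significantly whenever the mediator is included in the regression model".

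The only other tool offered is conditional and aimed at overall fit: "If we have sufficient power, the overall quality of the conceptual model can be tested using structural equation modeling". The text on mediation names no outcome scale or link, no test of the fall, no adjustment for common causes and no use of the repeated waves. Objective 1, by contrast, specifies mixed models with adjustment for baseline differences and for covariance within each ENS.

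The outcome type appears in the Sample Size section, where 100 patients per site (600 per wave) "will give us 80% power to detect 10% change in proportional outcomes (e.g. 50% to 60" percent), with a "two-sided test with 0.05 alpha" and an intra-class correlation of 0.005.

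**The concern.** The criterion says that the weight must fall significantly if mediation is present. Two things make that unsafe.

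- **A fall is not necessary.** In a logistic model the weight of a predictor changes when any strong predictor of the outcome is added, even one unrelated to the first. The weights with and without the mediator are then not comparable, and real partial mediation can leave little or no fall.
- **A fall is not sufficient.** Attitudes and usage are observed, not assigned. If the added variable is a common cause of predictor and outcome, the weight falls in the same way.

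At stake is the pathway from attitudes through usage to care, which is the subject of Objective 3. A real partial pathway could be reported as absent, or a confounded association reported as a pathway.

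**Working it through.** **The plan's own figure.** Design effect = 1 + (100 − 1) × 0.005 = 1.495. Effective number per wave = 600 / 1.495 = 401.3. Power for 50% against 60%, two-sided 0.05, waves treated as independent samples: 81.4%, against the stated 80%. The figure reproduces, but it concerns a change between waves and says nothing about power for mediation.

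**Inputs for the mediation check.** The Protocol gives no coefficients, so all values of a, b and c are assumptions. Model: X is standard normal; M = aX + e, with e of unit variance; logit P(Y = 1) = cX + bM. True mediated share = ab / (ab + c). Observed fall = (weight without M − weight with M) / weight without M. Clustering is ignored.

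**Step 1: large-sample logistic weights.**

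| (a, b, c) | True share | Without M | With M | Observed fall |
|---|---|---|---|---|
| (0.15, 1.5, 0.4) | 0.225/0.625 = 36% | 0.448 | 0.404 | 9.8% |
| (0.2, 2.0, 0.5) | 0.4/0.9 = 44% | 0.555 | 0.507 | 8.7% |
| (0.3, 1.5, 0.4) | 0.45/0.85 = 53% | 0.612 | 0.405 | 33.7% |
| (0.16, 1, 1) | 0.16/1.16 = 14% | 0.978 | 1.004 | −2.6% (rise) |
| (0.25, 2, 1) | 0.5/1.5 = 33% | 0.933 | 1.000 | −7.1% (rise) |
| (0.1, 1, 0.5) | 0.1/0.6 = 17% | 0.500 | 0.499 | about 0 |
| (0, 1.5, 0.5) | 0% | 0.357 | 0.500 | −40.1% (rise) |
| (0.5, 1, 0) | 100% | 0.418 | 0.004 | 99.1% |

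A repeat of the first three rows gave 9.4%, 9.3% and 34.5%, and of the seventh a rise of about 41%.

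**Step 2: the mechanism.** Without rescaling, the weight without M would be c + ab. The fitted weight is smaller by a factor k that depends mainly on b:

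- b = 1: 0.978/1.16 = 0.84 and 0.834/1.00 = 0.83 (the latter from a = 0, c = 1).
- b = 1.5: 0.448/0.625 = 0.72 and 0.357/0.5 = 0.71.
- b = 2: 0.555/0.9 = 0.62 and 0.933/1.5 = 0.62.

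The weight with M is about c, so the observed fall is about 1 − (1 − share)/k. It vanishes when the share is about 1 − k: roughly 16% at b = 1, 28% at b = 1.5 and 38% at b = 2.

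**Step 3: moderate mediators.** Logistic fits, true share against observed fall:

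- (0.3, 0.3, 0.1): 47% against 47%.
- (0.3, 0.5, 0.2): 43% against 40%.
- (0.3, 0.7, 0.2): 51% against 46%.
- (0.15, 0.5, 0.15): 33% against 29%.

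Since exp(0.7) = 2.0, the distortion is small for mediator odds ratios up to about 2 per residual standard deviation. The strong cases in Step 1 have odds ratios of exp(1) = 2.7, exp(1.5) = 4.5 and exp(2) = 7.4.

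**Step 4: linear scale.** Linear fits to data from the fourth, fifth and sixth rows of Step 1 give falls of 13.7%, 33.4% and 16.8%, matching the true shares. With no mediation (0, 1, 1) the linear weight does not change, while the logistic weight goes from 0.834 to 0.995.

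**Step 5: study-sized samples.** 200 trials per case, 150 bootstrap resamples each; standard error at most √(0.25/200) = 3.5 points. Percentage of trials with a significant fall in the logistic weight, against a significant product ab:

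| n | (a, b, c) | True share | Fall | Product |
|---|---|---|---|---|
| 600 | (0.16, 1, 1) | 14% | 0.5% | 98% |
| 600 | (0.25, 2, 1) | 33% | 0% | 100% |
| 600 | (0.3, 1, 1) | 23% | 53% | 100% |
| 600 | (0.5, 2, 1) | 50% | 74% | 100% |
| 600 | (0.5, 1, 0) | 100% | 100% | 100% |
| 120 | (0.3, 1, 1) | 23% | 16.5% | 89% |
| 120 | (0.5, 1, 0) | 100% | 98.5% | 100% |

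Here 120 is about 20 users at each of 6 sites.

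**Step 6: mediator or common cause.** With the correlation of X and M set at 0.5, b = 1 and c = 0, the logistic weight goes from 0.435 to 0.005 when M is a mediator and from 0.429 to −0.003 when M is a common cause. The linear weights go from 0.499 to −0.001 and from 0.500 to 0.001. With c = 0.5 the logistic weights go from 0.871 to 0.500 and from 0.872 to 0.501. The pairs cannot be told apart on either scale.

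**The case against.** A reader might infer that the Protocol treats a fall as proof of mediation. It does not say so. It speaks of potential mediation, its conditional runs from mediation to a fall, and the Hypothesis section says that the work is guided by evaluation questions rather than scientific hypotheses. This stands. What remains is that the conditional itself is wrong in general, and that no other mediation criterion is offered.

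A reader might also infer that the analysis will give wrong answers. That goes too far. No link function is named, and a SAP that is not at hand may fix one. Proportions appear in the sizing text, not in Objective 3, and satisfaction or attitude scales need not be binary. The masking needs a logit-type model, a strong mediator and a sizeable direct effect. Full mediation, the nearest reading of a mediator being responsible for the relationship, is found. All of this stands and limits the first half of the point to a conditional one. It does not touch the second half, since confusion with a common cause arises on every scale.

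It is also tempting to require lagged waves throughout, because five waves are collected and the chain is ordered. The Sample Size section does not support that: patients may be different people at each wave, patient data reach the evaluation center de-identified, abstraction patients need not be survey patients, and no link between users and patients is described. Only users are said to be likely to recur.

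Finally, direct estimation of the indirect effect is no cure for confounding. That is correct, and it is why the assumptions must be stated.

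**Conclusion.** The point holds in limited form. As a general statement, the criterion in Objective 3 is neither necessary nor sufficient for mediation.

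- **Not necessary**, if binary outcomes are analysed by logistic regression and the mediator predicts the outcome strongly. Under assumed odds ratios of 4.5 and 7.4, true shares of 36% and 44% show as falls of about 9 to 10%. Under odds ratios of 2.7 and 7.4, shares of 14% and 33% show as rises. Up to an odds ratio of about 2 the loss is at most about 5 points in the cases tried, and it is absent on a linear or risk-difference scale.
- **Not sufficient**, on any scale, because a common cause gives the same fall.

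The sizes rest on assumed coefficients and ignore clustering. The point concerns how Objective 3 is analysed and worded; it does not affect the stated power.

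**What to change.** Replace the coefficient-reduction criterion in Objective 3:

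1. Estimate the indirect effect directly, on a collapsible scale (linear or risk difference) or as a product of coefficients, which avoids comparing weights from two logistic models. Name the scale.
2. Give a confidence interval that respects clustering by ENS, and adjust for ENS and measured baseline covariates. Where the predictor is itself an ENS characteristic, adjustment by ENS indicators would absorb it, so the adjustment must be chosen to suit.
3. State the assumptions of no unmeasured confounding and of time order.
4. Report results as exploratory and as consistent with mediation, not as establishing it.
5. Use lagged waves only where the same respondents can be linked, for example repeat users, and not as a general requirement.

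The cost is a change of wording, slightly more analysis work and more cautious conclusions. Unmeasured confounding remains.

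### Objective 3 takes a fall in the predictor's regression weight as the general sign of mediation; if a yes/no outcome is fitted by logistic regression, that sign can understate or miss partial mediation

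*Protocol*

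**What the plan says.** Protocol, Statistical Analysis, Quantitative Objective 3, sets out a chain: characteristics shape users' attitudes, attitudes affect system usage, usage affects service delivery, and delivery affects health. On simple associations it says: "Relationships between individual variables can be documented via correlations or via regression equations". For mediation, the outcome is regressed on the predictor in models with and without the mediator. The criterion has a condition, "If the mediator is in fact responsible for the relationship between the predictor and the outcome", and a consequence, "then the regression weight for the predictor will be reduced significantly whenever the mediator is included in the regression model". No outcome scale or link function accompanies it. A further option is conditional: "If we have sufficient power, the overall quality of the conceptual model can be tested using structural equation modeling".

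The Sample Size section quantifies one type of outcome only. For both the patient survey and the ENS data extraction it states: "A sample of 100 per site (N=600 per observation period) will give us 80% power to detect 10% change in proportional outcomes", with 50% to 60% as the example. That statement does not mention mediation, and Objective 3 does not mention proportions.

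**The concern.** Comparing a weight with and without a mediator assumes that both weights are measured in the same units. In least-squares regression they are, and the difference between them equals the indirect effect. In logistic regression they are not. Leaving out any variable that predicts the outcome shrinks the remaining log-odds coefficient toward zero, even if that variable is unrelated to the predictor (non-collapsibility). Putting the mediator in therefore does two opposing things: it removes the mediated part, which lowers the weight, and it undoes the shrinkage, which raises it. The two can cancel. This happens however well the measurements are ordered in time.

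The attitude-to-usage-to-delivery path is the core of the conceptual model. If the outcome is yes/no and modelled by logistic regression, the stated criterion could lead the evaluation to report that attitudes do not work through usage, or work through it only slightly, when they do.

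**Working it through.** **Inputs from the protocol.** The with/without comparison and its criterion come from Objective 3. The yes/no outcome type, the 50% and 60% rates, N=600 per period, two-sided 0.05 and ICC 0.005 come from Sample Size. The protocol gives no path strengths, so every slope below is an assumption.

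**The plan's own figure.** Design effect = 1 + 99 × 0.005 = 1.495. Effective n = 600/1.495 = 401 per period. Power for 50% against 60% is then 81.4%, which agrees with the stated 80%. This figure does not concern mediation, and nothing below disputes it.

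**Model A: standardized predictor and mediator, outcome about 50%.** X is standard normal, M = aX + √(1−a²)·e, and logit P(Y=1) = cX + bM.
- The weight with M is c.
- The true mediated share on the log-odds scale is ab/(ab+c).
- The weight without M is the value t that solves E[X·(P(Y=1|X) − expit(tX))] = 0, evaluated by numerical quadrature.
- The apparent share is (t−c)/t.

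| a | b | c | True share | Weight without → with M | Apparent share |
|---|---|---|---|---|---|
| 0.2 | 1.5 | 1.0 | 0.30/1.30 = 23% | 0.949 → 1.000 | none (rises) |
| 0.3 | 1.5 | 1.0 | 0.45/1.45 = 31% | 1.075 → 1.000 | 7% |
| 0.3 | 1.5 | 0.5 | 0.45/0.95 = 47% | 0.696 → 0.500 | 28% |
| 0.3 | 1.0 | 0.3 | 0.30/0.60 = 50% | 0.506 → 0.300 | 41% |
| 0.3 | 0.5 | 0.5 | 0.15/0.65 = 23% | 0.619 → 0.500 | 19% |
| 0.3 | 1.5 | 0 | 100% | 0.326 → 0 | 100% |

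The first row shows the mechanism. On the scale of the full model the total effect is c + ab = 1.30. Omitting M shrinks it to 0.949, a factor of 0.949/1.30 = 0.73. That shrinkage more than offsets the mediated 0.30.

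**The same data on a linear (risk-difference) scale.** Row 1: 0.199 → 0.153, a fall of 0.046/0.199 = 23%. Row 3: 0.157 → 0.083, a fall of 0.074/0.157 = 47%. Both recover the true share.

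**Model B: the protocol's own rates.** X is binary and M = aX + N(0,1), with outcome rates of 50% and 60%. The weight without M is ln(1.5) = 0.405 in every case, and the mediated share is taken on the risk scale.
- b=2, a=0.1: 0.405 → 0.468 (rises), with 30% of the 10 points mediated.
- b=1, a=0.1: 0.405 → 0.390, an apparent 0.015/0.405 = 4%, with 20% mediated.
- b=1, a=0.2: 0.405 → 0.290, an apparent 0.115/0.405 = 28%, with 40% mediated.

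**The case against.** The strongest reply is that logistic regression appears nowhere in the protocol. Objective 3 speaks only of regression, a linear fit to the same yes/no outcome behaves as the protocol says, and the link function is normally left to a SAP, which is not at hand. This stands in part: the problem is conditional on a modelling choice. It does not remove the point, because the criterion itself is stated, without limit, in terms that are untrue for the usual model of a yes/no outcome.

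Second, the condition that the mediator be responsible for the relationship can be read as complete mediation, where the logistic weight does go to zero. That reading is possible. But a weight that is reduced, rather than eliminated, naturally covers partial mediation too, and that is where the rule can go wrong.

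Third, the cases with a flat or rising weight are demanding. Log-odds of 1.5 and 1.0 per standard deviation are odds ratios of about 4.5 and 2.7. The protocol says that usage will affect delivery but not how strongly. This stands; with moderate values the understatement is mild.

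Two stronger readings are tempting and are not supported. A reader might infer that the rule fails for the study's outcomes because they are proportions. Proportions are the sizing example for two patient components, Objective 3 does not say that its outcomes are binary, and satisfaction or health status may be continuous. A reader might also infer how rarely 600 patients would reveal mediation. Attitudes and usage belong to users, about 20 × 6 = 120 per wave, and no link from users to individual patients is described. A detection rate based on 600 independent attitude values would describe data that the protocol does not.

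The structural equation model is no safeguard: it is optional, depends on power, and is meant to test the model as a whole.

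**Conclusion.** The point holds as a conditional one. The criterion is stated too generally. With a yes/no outcome and logistic regression it can understate partial mediation, from slightly (23% shown as 19%) to substantially (47% shown as 28%). With a strong mediator-outcome effect, a sizeable direct effect and a weak predictor-mediator path, the weight can stay flat or rise. These sizes rest on assumed path strengths and, in the standardized illustration, an outcome near 50%. The calculations ignore clustering, which does not alter the direction of the result. Linear models, risk-difference models and complete mediation are unaffected, and so are the other objectives and the sample size. The wording should be changed because a better criterion costs little.

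**What to change.** In Objective 3, replace the reduced-weight criterion with a direct estimate of the indirect effect: either the product of the predictor-to-mediator and mediator-to-outcome paths, or the natural indirect effect on the risk-difference scale. Report it with a bootstrap interval that respects the clustering of the data. For binary outcomes, show any comparison of models with and without the mediator only on the risk-difference scale, and do not compare logistic weights between the two models. The with/without comparison can stay for continuous outcomes in linear models. The cost is a revised paragraph and slightly more analysis work in standard software, with no new data.
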